### Circulating immune cells

CIC analyses will be performed using enriched peripheral blood mononuclear cells (PBMCs) stained for multi-parametric FACS analyses. PBMCs will be analyzed to define and characterize various immune cell populations and to determine the expression profiles of T-cells, cytotoxic T-cells, T-regulatory cells (T-regs), natural killer (NK) cells, B-cells and immune checkpoint inhibitor. A second tube will be used to determine the monocytes/macrophages expression profile. The Zombie red™ Fixable Viability kit will be used to exclude dead cells. Samples will be analyzed by Beckman Coulter Gallios Flow Cytometry, and data will be collected with the Kaluza acquisition software and analyzed with the Kaluza software.

### Circulating microbiota

The number of 16S rRNA gene copies, which reflect the circulating DNA microbiota, will be measured in plasma by qPCR following the protocol previously published [17]. DNA will be extracted from 200 μL of plasma with the QIAcube® automatic extractor (Qiagen, Courtaboeuf, France) and the QIAamp MinElute ccfDNA® kit (Qiagen, Courtaboeuf, France) as per the manufacturer's instructions. The amplified region will have a size of 199 bp, and the V5 region of the 16S rRNA gene will be targeted. The 16S rRNA gene real-time PCR will be performed twice on two biological duplicates for each sample. A negative control using molecular biology grade pure water will be included. A standard curve will be created from serial dilutions of synthetic DNA containing known copy numbers of the template. The assays will be conducted using a LightCycler 480 II (Roche). Absolute quantification analysis will be performed with the Lightcycler 480 software (Roche), version 1.5, following the manufacturer's recommendations.

Markers such as LPS binding protein (LBP) and soluble cluster of differentiation 14 (sCD14) will be used as biomarkers to indicate indirect microbiota translocation and gut inflammation. The Intestinal fatty acid binding protein (I-FABP) will be measured to study intestinal permeability. LBP, sCD14, and I-FABP will be evaluated using an Enzyme-Linked ImmunoSorbent Assay (ELISA) in accordance with the manufacturer’s recommendations. The LBP plasma level will be measured using the LBP Soluble ELISA kit (Enzo Life Sciences, Villeurbanne, France), the sCD14 plasma level using the soluble CD14 (human) ELISA kit (Enzo Life Sciences, Villeurbanne, France), and the I-FABP plasma level using the Human I-FABP ELISA kit (Hycult Biotech, Uden, the Netherlands).

### Biobanking

Samples collected as part of the research will constitute a plasma, platelets, CTC and PBMC library to meet the objective of "Constituting a unique *LB* biobank for PDAC to optimize biomolecular knowledge on PDAC at different stages” under the responsibility of the coordinating investigator ([name]). This collection is made in accordance with the current regulations and will be declared to the regulatory authorities. Samples will be stored at the LCCRH-Liquid Biopsy laboratory, an approved laboratory, at—80 °C and liquid nitrogen for plasma and cells, respectively.

### Statistical analysis

In this project, the first type of machine learning model we will train is random forests. These will be used to predict whether a patient will develop pancreatic cancer based on all measured markers and associated health data. The dataset collected in this project will be divided into three different subsets: a training set (60% of the samples), a test set (20% of the samples), and a validation set (20% of the samples). A stratified sampling approach will be used to ensure that each class is accurately represented in each set, especially if an imbalance between classes is present in the original dataset. The training and test subsets will be used to train the machine learning algorithms, while the validation subset will be used to ensure that the model is generalizable (i.e., it can accurately classify future samples that may be collected). We will use the out-of-bag error method (a bootstrapping procedure that trains the models on multiple subsets of the predictor variables) to quantify the relative contribution of each variable to the model's performance. In addition, the performance of each model will be quantified by calculating its accuracy, precision, and area under the curve (AUC). In the performance of the random forest models is not satisfactory, the same approach will be used, but this time using XGboost and artificial neural network models instead. This approach allows the complexity of the model to be gradually increased, with the aim of forming a parsimonious model with a good ability to distinguish between healthy and cancer patients. The performance of all models trained during this project will be compared to a multiple logistic regression model as a baseline model.

We will also explore the results of machine learning models in the inferential framework. Using generalized linear models, we will compare the mean of each marker retained by the best machine learning models, while controlling for confounding variables (e.g., age…). This approach will quantify the differences in markers between healthy and cancer patients and identify markers that may not be statistically significantly different between the two groups but still contribute to good machine learning performance (those variables are called "weak predictors").

Indeed, in some cases, the combination of several "weak predictors" with a machine learning model can lead to good prediction performance. This will provide valuable information on the number and type of markers to be retained for future diagnosis.

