## Abstract

**Background:**

Pancreatic cancer, predominantly characterized by ductal adenocarcinoma (PDAC) accounts for 90% of cases and is the fourth leading cause of cancer-related deaths globally. Its incidence is notably increasing. This poor prognosis is primarily due to late-stage diagnosis (approximately 70% to 80% of patients are diagnosed at an advanced stage), aggressive tumor biology, and low sensitivity to chemotherapy. Consequently, it is crucial to identify and develop a simple, feasible and reproducible blood-based signature (i.e., combination of biomarkers) for early detection of PDAC.

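### Markers are ranked within a single 60/20/20 division of the samples, so the markers named depend partly on the draw and the held-out samples do not inform their selection

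*Protocol article*

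**What the plan says.** The protocol article's Statistical analysis section says that the collected data "will be divided into three different subsets: a training set (60% of the samples"), with 20% each for test and validation. On how the division is drawn it says: "A stratified sampling approach will be used to ensure that each class is accurately represented in each set". It describes one division and mentions no repeat.

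On which samples train the models, the section adds: "The training and test subsets will be used to train the machine learning algorithms". The validation fifth is kept to check generalisability.

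Markers are assessed by out-of-bag error in the random forest, in order to "quantify the relative contribution of each variable" to how well the model performs. If the forest performs poorly, XGBoost and neural networks follow. Markers kept by the best models go into generalised linear models, and the section ends by saying that this work will inform "the number and type of markers to be retained for future diagnosis".

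Three other places matter:
- The Circulating proteins section gives a library of 3000 assays.
- The Design section gives 295 discovery and 60 validation subjects.
- The abstract's Background asks for a "simple, feasible and reproducible blood-based signature".

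**The concern.** The main objective in Aims of PANLIPSY is to define a signature from the most relevant analytes, so the list of markers is itself a deliverable. When candidates far outnumber subjects, many markers have nearly equal importance, and which of them reach the top depends on who falls into the training part.

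Nothing described in the section removes this dependence:
- Stratification balances the classes but does not fix which subjects are drawn.
- The bootstrap inside a forest works only on the subjects it was given.
- The validation phase tests the one combination already defined. It does not ask whether the same markers would be chosen again.

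Two things are at stake. The article would report a list with no indication of which members are firm and which are borderline. And 20% to 40% of the discovery subjects would contribute nothing to choosing the markers.

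**Working it through.** **The plan's own figure.** The Sample size justification gives a 95% interval width of 0.118 for AUC 0.85 with 85 v 85. By Hanley-McNeil, Q1 = A/(2−A) = 0.85/1.15 = 0.7391 and Q2 = 2A²/(1+A) = 1.445/1.85 = 0.7811.

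Var = [A(1−A) + 84(Q1−A²) + 84(Q2−A²)]/(85×85) = [0.1275 + 84×0.0166 + 84×0.0586]/7225 ≈ 0.00089

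Half-width = 1.96×√0.00089 ≈ 0.0585, so the width is 0.117. The figure reproduces. It concerns the precision of one AUC and says nothing about marker selection.

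**Size of the ranking set.** Taking the 295 discovery subjects (185 PDAC, 110 non-cancer):
- 60%: 0.6×295 = 177
- 80%: 0.8×295 = 236
- hold-out: 0.2×295 = 59

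If the data set means all 355, the first two are 213 and 284.

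**Check 1: agreement of two draws, t-statistic ranking.** Assumptions: 185 v 110, 3000 candidates, 20 true markers, top-20 list.

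| Standardised difference | Shared at 60% | Shared at 80% |
|---|---|---|
| 0.4 to 0.6 | 6–13 of 20 (30–65%) | 11–17 of 20 (55–85%) |
| strong (0.8) | about 18 of 20 | about 19 of 20 |

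**Check 2: agreement of two draws, random forest.** Assumptions: N = 295, 3000 candidates in correlated blocks, 50 true markers, top-20 list, 4 replicates per setting. Impurity importance stands in for out-of-bag importance.

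| Differences | Two 60% draws | Two 80% draws | Same draw, new forest seed (60% / 80%) |
|---|---|---|---|
| 0.2–0.6 | 35% | 60% | 74% / 75% |
| 0.3–0.8 | 66% | 81% | 81% / 89% |
| 0.5–1.0 | 69% | 82% | 84% / 85% |

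The last column shows that part of the disagreement is forest noise. At 80% with strong markers it accounts for most of it. Agreement also stays below complete here because 50 true markers compete for 20 places. With N = 355 the shares are 46–75% at 60% and 74–80% at 80%.

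**Check 3: where the gain in true markers comes from.** Assumptions: 185 v 110, 3000 candidates, 20 true markers, top-20 list. Entries are true markers found.

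| Ranking | One 60% draw | One 80% draw | Averaged over repeats | One fit on all 295 |
|---|---|---|---|---|
| Forest, difference 0.5 | 9.7 | 11.8 | 14.1 | 14.5 |
| t-statistic, differences 0.4 / 0.5 / 0.6 | – | – | 12.4 / 16.2 / 18.4 | 12.4 / 16.4 / 18.5 |

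Averaging over repeats finds no more true markers than one fit on all the samples. The gain over a single draw comes from using all discovery subjects.

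**Check 4: what the repeats add.** With t-statistic ranking at 85 v 85, two single 60% draws share 34–71% of the list. Two independent runs of selection frequency over 100 draws share 87–97%. This is stability to the choice of split within one data set.

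**The case against.** The strongest reply has five parts.

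- **The training share is unclear.** The section supports 80% as readily as 60%. This stands: at 80% the lists agree clearly better, and any statement of size must show both.
- **The article does not say that the division is never repeated.** This also stands as a limit. A full analysis plan could add repeats. But the article states the division, its proportions, its stratification and the ranking method, and its plain reading is one division.
- **No top-20 rule appears, effect sizes are not given, and a library of 3000 need not mean 3000 model inputs.** Correct. In forest simulations with 4 to 8 of 20 shared at 60%, held-out AUC was 0.63–0.69, below the planning value of 0.85. At AUC 0.91 the lists shared about 15 of 20. The direction is robust; the size is not.
- **Correlated markers can replace one another, so the AUC may not suffer.** Correct. In a setting with 40 strong markers (AUC 0.97), draws shared only 13.8 of 20, yet 19.9 of the 20 chosen were true.
- **Resampling all discovery subjects uses up the discovery hold-out,** which is the only held-out test that can include benign disease, because the validation cohort has none. This stands unless the left-out part of each repeat is scored.

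A reader might infer that the panel is mainly an accident of the random seed, or that the signature will fail in new patients. The documents support neither. The number of true markers missed reflects the held-out samples, the abstract's call for reproducibility does not promise identical membership under another split, and the defined combination is tested blindly in separate subjects.

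**Conclusion.** The concern holds in a limited form. As described, the markers named depend partly on one random division, and the samples held out do not inform the choice. Two draws share roughly a third to two thirds of a top-20 list at 60% and about half to four fifths at 80% when markers are modest. When markers are strong and no more numerous than the places on the list, the lists nearly agree under a simple ranking; forest rankings agree less.

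These figures rest on assumed effect sizes, number of true markers, correlation, panel length and importance measure, and on reading the data set as the 295 discovery subjects. Using all discovery samples is what recovers more true markers. Repeats add stability and a selection frequency for each marker. Neither demonstrates reproducibility in new patients, and no loss of AUC is claimed.

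**What to change.** In the Statistical analysis section, replace the single 60/20/20 division with repeated stratified splits (for example 100) or repeated nested cross-validation of the discovery samples, and state which share trains.

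1. Do the ranking and any tuning inside each training part only.
2. Score the left-out part of each repeat for accuracy, precision and AUC, including the subjects with benign disease.
3. Report each marker's selection frequency, and fix the retention cut-off in advance.
4. Fit the panel once on all discovery samples, lock it, and test it in the 30 v 30 validation cohort, which stays untouched until then.

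The cost is computing time and a few sentences, with no extra patients or assays. The downside is that the fixed 20% discovery hold-out gives way to left-out estimates. In return every benign case can be scored out of sample, where one proportional 20% hold-out would contain about 0.2×25 = 5. The change has to be made before the panel is locked.

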### Circulating proteins

O-link PEA is an immunoassay-based technology that relies on matched antibody pairs for dual recognition of proteins (biomarker) in biological samples. The two matched antibodies, which target the same protein, are conjugated to unique DNA oligonucleotides with a stretch of sequences complementary to each other. When the antibody pair binds to the target protein, complementary DNA oligonucleotides hybridize, and get extended and amplified by DNA polymerase. Each amplified DNA pair contains unique barcode sequences that are read using qPCR. The library includes 3000 highly validated protein assays that cover all major biological pathways.

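### Marker means are tested only for markers the model retained, and no samples unused for selection are assigned; if the selection samples are reused, the p-values and differences are biased

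*Protocol article*

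**What the plan says.** Under Statistical analysis, random forests are trained first on all measured markers and health data, with XGBoost and neural networks as fallbacks. A second step follows: "We will also explore the results of machine learning models in the inferential framework". In it, "we will compare the mean of each marker retained by the best machine learning models, while controlling for confounding variables", age being the example given. Its stated purposes are to quantify group differences and to "identify markers that may not be statistically significantly different between the two groups but still contribute to good machine learning performance"; the latter are named weak predictors. The section then says of the exercise: "This will provide valuable information on the number and type of markers to be retained for future diagnosis".

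The same section splits the data 60/20/20. The training and test parts (80%) serve to train the algorithms; of the remainder it says "the validation subset will be used to ensure that the model is generalizable". The marker comparison is tied to none of the three. The separate 30 v 30 cohort under Validation phase is assigned to blind classification.

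On the number of candidates, Circulating proteins says: "The library includes 3000 highly validated protein assays that cover all major biological pathways". The article does not say how many of these enter the model, how many markers will be retained, or what alpha and multiplicity rule apply to the marker comparisons.

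**The concern.** A marker is retained because it helps to separate cancer from healthy samples. The GLM then asks whether its mean differs between cancer and healthy samples. On the samples that drove retention, the question has been partly answered in advance: a noise marker that got through did so because it happened to differ there. Its p-value no longer has its nominal meaning, and its estimated difference is too large on average.

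Two outputs are affected. The sort into significant markers and weak predictors moves noise markers into the first class. The quantified differences, offered as information on which markers to carry forward, are overstated. Restricting the tests to retained markers is a stated choice. It gives valid p-values only in samples that played no part in selection.

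**Working it through.** **The plan's own figure.** The article gives no figure for the marker tests. The nearest is under Sample size justification, which supplies the group sizes: 85 v 85, AUC 0.85, 95% interval width 0.118. The Hanley-McNeil variance reproduces it:

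- Q1 = A/(2−A) = 0.85/1.15 = 0.7391; Q2 = 2A²/(1+A) = 1.445/1.85 = 0.7811; A² = 0.7225.
- Var = [0.1275 + 84(0.7391−0.7225) + 84(0.7811−0.7225)]/85², so SE = 0.02987.
- Half-width = 1.96 × 0.02987 = 0.0585, which rounds to 0.059; twice 0.059 is 0.118.

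That calculation concerns the AUC and says nothing about individual markers.

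**Why selection matters.** Among 3000 null markers, 3000 × 0.05 = 150 reach p<0.05 by chance. A procedure that keeps the 20 that separate the groups best draws largely from those 150. At 85 v 85, an unadjusted two-sample test reaches p<0.05 only if the observed difference is at least 1.974 × √(2/85) = 0.30 SD. A null marker called significant therefore reports at least that much where the truth is zero.

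**Simulation inputs.**

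- From the article: 85 v 85; 3000 candidates as the library size; 80% of samples used for training and test; adjustment for age.
- Assumed: independent Gaussian null markers; ranking by random-forest importance (300-500 trees) with the top k retained; linear model on group and age; two-sided 0.05; no multiplicity adjustment.
- Varied because unstated: number retained and number of candidates.

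**Results:** share of retained null markers with p<0.05.

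| Candidates | Retained | Tested on selection samples | Tested on all samples | Tested on held-out 20% |
|---|---|---|---|---|
| 3000 | 10 | 93% | 84% | 3% |
| 3000 | 20 | 83% | 70% | 3% |
| 3000 | 50 | 67% | 52% | 3% |
| 3000 | 100 | 52% | 40% | 4% |
| 3000 | 300 | 30% | 25% | 5% |
| 3000 | 1000 | 13% | 12% | 5% |
| 100 | 5 | 61% | 46% | 5% |
| 100 | 10 | 41% | 30% | 4% |
| 100 | 20 | 24% | 20% | 4% |
| 30 | 5 | 27% | 21% | 5% |
| 30 | 10 | 15% | 12% | 5% |

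Replicates: 15 for 3000 candidates, 40 for 100, 60 for 30. For the 20-of-3000 row that is 300 retained markers, so the standard error of 83% is about √(0.83 × 0.17/300) = 2 points.

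**Variants**, 20 retained of 3000 (selection / all / held-out):

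- 20 true markers (d = 0.7) among the 3000: 88% / 67% / 4% of the retained nulls.
- All PDAC stages, 185 v 85: 81% / 66% / 4%.
- Selection on the 60% training part only: 83% / 56% / 7% (8 replicates).

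Across all null markers, retained or not, about 5% reach p<0.05 in every scenario.

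**The case against.** The strongest reply is that the circularity is inferred. The article names no samples for the comparison, and both a 20% validation subset and an independent 30 v 30 cohort exist that could serve. An article may leave that detail to a full plan. This stands to the extent that one cannot say the tests are circular, only that the text, followed as written, leaves them open to it. What remains is that testing only the retained markers, sorted by significance, is stated, while every subset is given a different job.

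A reader might infer that most null markers would look significant. They would not: about 5% of all null markers do. Most applies only to null markers that were retained. With 3000 candidates it holds up to about 100 retained if the selection samples are tested, and about 50 if all samples are tested. The stated aim of a parsimonious model makes a small panel plausible but fixes no size. Likewise, 3000 is the size of the assay library; the article does not say that all of them enter the model. With 100 or 30 candidates the bias is smaller, though still present.

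A reader might also infer that the step decides which markers are kept, and so certifies noise. The text does not say so. The model does the selecting, non-significant retained markers are not discarded, and the comparison is said only to inform future choices. It is introduced as exploration, it is not a listed endpoint, and the signature itself is checked blindly in an independent cohort. This limits the consequence, but it does not make the p-values valid for the use the section gives them.

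**Conclusion.** The concern holds in conditional form. The article restricts the marker comparisons to markers chosen on the same contrast, relies on statistical significance, and assigns no unselected samples. If the selection samples or all project samples are used, the p-values are far too small and the differences too large for retained noise markers. With 3000 candidates and 80% of samples used for selection, the simulated share reaching p<0.05 runs from 12% (1000 retained) to 93% (10 retained), against about 3-6% in the held-out 20%. The figures rest on independent Gaussian markers, random-forest ranking and unadjusted 0.05 tests. Correlation among proteins, which was not simulated, would alter the percentages; I would not expect it to remove the bias. The trial's listed endpoints are not touched by this step. The damage is confined to the marker-level inference and to what is read from it about a future test.

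**What to change.** - In the discovery data, fit the adjusted GLM to every measured marker with Benjamini-Hochberg FDR control, and base the weak-predictor label on those results.
- Give p-values and effect sizes for the retained markers only from samples not used for selection. The 30 v 30 validation cohort is suitable if it is kept out of the 60/20/20 split. Apply Holm or Benjamini-Hochberg control there.
- If neither is wanted, report the retained-marker differences descriptively, without p-values. That is an acceptable alternative.

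No extra patients or assays are needed. The cost is fewer significant markers and low power at 30 v 30. By a two-sample t-test, power is about 48% at d = 0.5 and 76% at d = 0.7 at two-sided 0.05. At Holm's first step for 20 markers (0.05/20 = 0.0025), it falls to about 12% and 34%. The plan should therefore say that non-significance in the validation cohort is not evidence of no difference, and should report intervals alongside.

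### Retained but not significant does not make a marker a useful weak predictor: contribution has no null reference, so that list can be mostly noise

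*Protocol article*

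**What the plan says.** All points are in the Statistical analysis section of the protocol article unless stated otherwise.

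- The forest predicts cancer "based on all measured markers and associated health data". The Circulating proteins section says of the protein platform: "The library includes 3000 highly validated protein assays that cover all major biological pathways".
- Contribution is measured by out-of-bag error, described as follows: "We will use the out-of-bag error method (a bootstrapping procedure that trains the models on multiple subsets of the predictor variables". Its purpose is "to quantify the relative contribution of each variable".
- If the forest does not perform well enough, "the same approach will be used, but this time using XGboost and artificial neural network models instead". Logistic regression is the baseline for comparison.
- Generalized linear models then "compare the mean of each marker retained by the best machine learning models", with adjustment for confounders. The stated purpose is to quantify differences and to "identify markers that may not be statistically significantly different between the two groups but still contribute to good machine learning performance". Such markers are named weak predictors.
- The section ends: "This will provide valuable information on the number and type of markers to be retained for future diagnosis".
- The Validation phase section has the chosen combination classify 30 resectable PDAC patients and 30 healthy controls blind.

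**The concern.** A marker becomes a weak predictor on two grounds: it is among those kept as contributing, and its group difference is not significant. The second is no evidence of usefulness, because a marker unrelated to disease is normally non-significant. All the evidence must therefore come from the first, and contribution is described only in relative terms. In a ranking some markers always come out ahead, whether or not they carry signal.

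This is not the familiar problem of testing selected markers on the data that selected them. It would remain if the linear models were fitted to fresh subjects with valid p-values.

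The first main end-point in the Abstract is a signature of the most relevant markers, and this step is meant to inform the choice for future diagnosis. A list that is largely noise would send uninformative assays forward and work against the section's own aim of a parsimonious model.

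**Working it through.** **The plan's own figure.** The only computed precision figure (Sample size justification) is a 95% CI width of 0.118 for an AUC of 0.85 with 85 v 85. The Hanley-McNeil variance is [0.1275 + 84(0.7391 − 0.7225) + 84(0.7811 − 0.7225)] / 85² ≈ 0.00089. The half-width is 0.0585 and the width 0.117, so the figure reproduces. It concerns the whole signature and does not bear on single markers.

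**Inputs.** There are 3000 candidate proteins if the full library enters. The training share is 60%:
- 0.6 × 170 = 102 (51 v 51) for resectable PDAC against healthy controls;
- 0.6 × 270 = 162 (111 v 51) for all discovery PDAC against healthy controls;
- 0.6 × 295 = 177 (111 v 66) if benign disease joins the controls.

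No significance level is given; two-sided 0.05 is assumed.

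**Non-significance alone.** On fresh data, 0.95 × 3000 = 2850 of 3000 noise markers would be non-significant.

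**Simulation.** Independent normal markers, random forest with √3000 variables tried per split, out-of-bag permutation importance, and an unadjusted t-test in place of the linear model, on the training subjects. There were 500 trees (2000 in the first row) and 3 to 6 runs per row. Number of true markers, effect sizes (in SD) and cut-offs are assumptions.

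| True markers, effect | Training | Noise among all 3000 | Noise in weak list, importance > 0 | Noise in weak list, top 50 |
|---|---|---|---|---|
| 10, 0.8 | 51 v 51 | 99.7% | 100% of 1194 | 100% of 20.7 |
| 20, 0.8 | 111 v 66 | 99.3% | 100% of 937 | 100% of 19.2 |
| 100, 0.3 | 51 v 51 | 96.7% | 97% of 768 | 96% of 22.2 |
| 300, 0.4 | 51 v 51 | 90% | 94% of 694 | 82% of 9.8 |
| 900, 0.4 | 51 v 51 | 70% | 79% of 548 | 75% of 2.0 |
| 900, 0.3 | 111 v 51 | 70% | 78% of 796 | 58% of 6.0 |
| 1500, 0.3 | 51 v 51 | 50% | 56% of 572 | 45% of 5.0 |

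The third column is (3000 − true markers) / 3000. Under importance above zero, the weak list holds at least as large a share of noise as the full candidate set. Under a top-50 cut it is at most modestly better, on very short lists when signal is dense. The label adds little or nothing to what was known before the forest was fitted.

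**With p-values from fresh subjects** (400 trees, 30 true markers at 0.5 SD, so 99% noise overall): at 111 v 66, 972 of 974 weak predictors were noise under importance above zero, and 38 of 39.5 (96%) under top 50. At 51 v 51, top 50 gave 43 of 44.5 (97%), and a separate simulation gave 41 of 43 (95%). Independent data for the linear model does not cure the problem.

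**What validation can show.** With 20 true markers at 0.8 SD, a top-50 panel with about 38 noise markers reached a held-out AUC of 0.93, against 0.96 with its true markers only. A panel can pass while most of its members are noise.

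**The out-of-bag description.** Out-of-bag error comes from bootstrapping subjects and predicting those left out; subsampling predictors is a separate feature of the forest. Subsets of predictors alone leave no subject out of bag. A neural network has no native out-of-bag sample, and a standard XGBoost fit does not give this measure either. If the same approach includes the contribution step, it does not carry over.

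**The case against.** - *Retention is decided first, the step is introduced as exploratory, and the aim is parsimony.* True: a list of hundreds is not what the authors want. But the top-50 results show the same weakness under sparse signal, and the section still draws advice on markers from the label.
- *The retention rule may stand in an analysis plan that is not shown.* This stands: a missing cut-off alone would be no finding. What can be faulted is the stated inference, which a cut-off on a relative ranking would not repair.
- *The retained set also holds significant markers, which feed the advice too.* This stands. With 300 to 900 true markers the whole top 20 held only 8 to 18% noise.
- *A forest without any signal would be judged unsatisfactory and replaced.* This also stands, so the conclusion does not rest on a no-effect scenario.
- *The out-of-bag sentence is a slip.* Probably. It does say bootstrapping, so a reader should not infer that importance will be measured on the subjects used for fitting, where 78 to 93% of pure-noise markers looked positive in simulation. The same approach may also mean only the data split and performance measures. The wording still needs correction.
- *The simulation is thin.* Runs were few and markers independent; correlated proteins would change the figures. The argument about non-significance does not depend on them.

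**Conclusion.** The concern holds in a limited form. Retained and not significant, with contribution known only as a rank, does not distinguish a weak true marker from noise, so this step should not guide which markers to keep. The weak-predictor list was about 90 to 100% noise with 10 to 100 true markers among 3000. With 900 to 1500 it was about 55 to 80% noise under importance above zero, and 45 to 75% in the few non-significant markers of a top-50 list. These sizes rest on the assumptions stated with the simulation.

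Two stronger readings are not supported:
- A reader might infer that almost every noise marker would earn the label. Under importance above zero it was about 20 to 40%, and under a top-100 list about 0.4 to 2%. It neared 95% only when any use in a tree of a 2000-tree forest counted as retention.
- A reader might infer that the marker advice as a whole would be nearly all noise. The figures concern the non-significant part of the retained set, and they depend on a signal density that nobody yet knows.

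**What to change.** 1. Measure importance as the loss of AUC when a marker is permuted in subjects not used to fit the model. Do this in the same way for random forest, XGBoost, neural network and logistic regression. Judge it against a permutation null at a stated false-discovery level.
2. Describe non-significant retained markers as useful only if refitting the chosen model without them, as a set, lowers cross-validated AUC in the discovery data. Report the paired difference with its 95% CI.
3. Correct the out-of-bag sentence: subjects are resampled, and predictors are subsampled at splits.

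A harsher rule, keeping only markers that beat the largest importance among permuted copies, is not advised. In simulation it held noise to 1.5 markers or fewer, but kept only about 4 of 30 true markers at 0.5 SD and 21 of 30 at 0.8 SD. A false-discovery level lets the team choose that trade-off openly.

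The cost is analysis-plan wording and computing time, with no new patients or assays. The downside is a shorter list that may miss some truly weak markers.
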